#### Secondary outcomes

2.6.2

To address the second study objective, one or more questionnaires were included per lifestyle domain when a single instrument did not capture all relevant constructs. Furthermore, the secondary outcome measures focus on personal goals, general health and PD symptoms. The secondary outcomes of this study are presented in Table 1, including the constructs and used outcome measures. All questionnaires are patient reported outcomes, administered at baseline (T0), after 6 months (T1) and after 12 months (T2). Participants will receive the following questionnaires: health-related quality of life (EuroQol 5D-5L) (47–49), non-motor and motor aspects of PD in daily living (MDS-Unified Parkinson’s Disease Rating Scale-IB and -II) (50, 51), fatigue (Fatigue Severity Scale) (52), evaluation of lifestyle goals (Visual Analogue Scale) (53), diet quality (Dutch Healthy Diet Index 2015) (54), symptoms of anxiety and depression (Hospital Anxiety and Depression Scale) (55), physical activity (LASA Physical Activity Questionnaire) (56), insomnia (Insomnia Severity Index) (57), daytime sleepiness (Epsworth Sleepiness Scale) (58–60), general perceived self-efficacy (General Self-Efficacy Scale) (61, 62), disease and impairment acceptance (Acceptance of Disease and Impairments Questionnaire) (63), coping (Ways of Coping Questionnaire) (64, 65), and self-management (Patient Activation Measure) (66). Additionally, a wrist monitor (Empatica EmbracePlus) (67) will be worn 1 week at baseline (T0) and 1 week after 12 months (T2) to collect data on physical activity and sleep quality. Due to a limited number of available monitors, approximately two-thirds of the participants will wear the wrist monitor. The EmbracePlus uses electrodermal activity, photoplethysmogram (PPG), digital skin temperature and accelerometer sensors to collect data. Raw sensor data is accessible through an online dashboard. The EmbracePlus will be worn on the arm that is least affected by PD symptoms, to optimize monitoring of physical activity and minimize interference from symptoms such as tremor and bradykinesia.

**Table 1 tab1:** Overview primary and secondary outcome measures.

(Lifestyle) domain	Construct	Outcome measure	T0	T1	T2
General	Quality of life (primary outcome)	PDQ-39	**⨯**	**⨯**	**⨯**
	Health related quality of life	EQ-5D-5L	**⨯**	**⨯**	**⨯**
	Parkinson’s disease symptoms	MDS-UPDRS 1b & 2	**⨯**	**⨯**	**⨯**
	Fatigue	FSS	**⨯**	**⨯**	**⨯**
	Goal attainment	VAS	**⨯**	—	**⨯**
Nutrition	Diet quality	DHD15-index	**⨯**	**⨯**	**⨯**
Stress	Mood (anxiety and depression)	HADS	**⨯**	**⨯**	**⨯**
Exercise	Physical activity level	LAPAQ	**⨯**	**⨯**	**⨯**
	Physical activity	Wearable sensor	**⨯**	—	**⨯**
Sleep	Insomnia	ISI	**⨯**	**⨯**	**⨯**
	Sleepiness	ESS	**⨯**	**⨯**	**⨯**
	Sleep quality	Wearable sensor	**⨯**	—	**⨯**
Self-management	Self-efficacy	GSES	**⨯**	**⨯**	**⨯**
	Illness acceptance	ADIQ	**⨯**	**⨯**	**⨯**
	Coping	WCQ	**⨯**	—	—
	Self-management	PAM	**⨯**	**⨯**	**⨯**

T0 = Baseline measurement, T1 = 6 month measurement, T2 = 12 month measurement (end of intervention), PDQ-39, Parkinson’s Disease Questionnaire-39; EQ-5D-5L, EuroQol 5D-5L; MDS-UPDRS, MDS-Unified Parkinson’s Disease Rating Scale; FSS, Fatigue Severity Scale; VAS, Visual Analogue Scale; DHD15-index, Dutch Healthy Diet Index 2015; HADS, Hospital Anxiety and Depression Scale; LAPAQ, LASA Physical Activity Questionnaire; ISI, Insomnia Severity Index; ESS, Epsworth Sleepiness Scale; GSES, General Self-Efficacy Scale; ADIQ, Acceptance of Disease and Impairments Questionnaire; WCQ, Ways of Coping Questionnaire; PAM, Patient Activation Measure.

##### Cost-effectiveness

2.6.2.1

We will perform a cost-effectiveness analysis from a societal perspective. Data on the frequency and duration of healthcare service utilization will be collected through a questionnaire at T1 and T2. The healthcare services include, but are not limited to, the use of allied healthcare, hospital, social care services (e.g., physiotherapists, neurologist, social workers). The questionnaire allows participants to report additional healthcare disciplines that are not listed. In addition, the use of assistive devices purchased during the study period will be recorded, including whether these were reimbursed through insurance. Additionally, to expand the cost-effectiveness analysis beyond healthcare utilization, participants receive questions regarding their work and productivity status at all time points (T0, T1, T2). In this context, productivity refers to both labor force participation and on-the-job performance (68, 69). For each participant in the intervention group, the lifestyle coach will record the amount of guidance provided, the use of digital tools, and the extent of lifestyle coaching. These elements will be included in the economic evaluation. Specialized care (step 4) is evaluated using a questionnaire on healthcare utilization at T1 and T2. The QoL related outcomes resulting from the EQ-5D-5L questionnaire enables the derivation of utility scores and the estimation of quality-adjusted life years (QALYs), which will be incorporated into the cost-effectiveness analysis.

##### Informal caregiver questionnaires

2.6.2.2

To be able to provide more detailed information for the (socio)economic analysis, we also include informal caregivers. They will be asked to fill out several questionnaires at T0, T1 and T2. The questionnaires that will be sent online include the Caregiver Strain Index (CSI) (70), the EQ-5D-5L questionnaire, and several questions about their working life (e.g., productivity, and informal care leave).

##### Process evaluation

2.6.2.3

To support future implementation, we will perform a process evaluation alongside the RCT. In this process evaluation we will evaluate the experiences of participants, lifestyle coaches and healthcare professionals. We will use questionnaires and interviews for this process analysis. For a process evaluation on the use of the lifestyle decision aid, various log data are collected (i.e., number of sessions, session duration).

### Participant timeline

2.7

Initially, an assessor from the research team sends an information letter and informed consent to potential participants. Two weeks later, a phone call is planned with the participants, during which they have the opportunity to ask questions. If they are still willing to participate, participants undergo a brief cognitive assessment over the phone to determine eligibility and informed consent will be obtained. Upon signing the informed consent, participants will receive multiple questionnaires for the baseline assessment which they can complete at home, at their own pace within two weeks. Reminder emails will be sent after two and four weeks, followed by telephone contact after six weeks if questionnaires remain incomplete. After the baseline questionnaires have been returned, participants will be randomly allocated into the control or intervention group. Within two weeks after completing the questionnaires participants will receive a package. Some participants will receive a package containing a wrist monitor. The monitor will be worn one week at the start of the study and one week at the end. The package also includes a “part 2.” After the week in which the participant has worn the monitor, part 2 of the package can be opened. It contains the randomization result and login details for the lifestyle decision aid. Participants can contact a helpdesk during office hours for additional information or guidance on how to use the wrist monitor or decision aid if needed. Participants who receive a package without wrist monitor can open the randomization results and login details for the lifestyle decision aid immediately.

The lifestyle coach will schedule an intake meeting with participants two weeks after the package delivery. The participants are required to complete the lifestyle decision aid before the meeting. Participants in the intervention group schedule a follow-up meeting with the lifestyle coach during the intake, typically one to three months later, based on personal goals and needs. The control group receives no further coaching after the intake.

All participants will receive a set of questionnaires at T1 and T2. Importantly, participants will not be required to visit the research location at Radboudumc. All research procedures can be performed from their own home.

### Sample size

2.8

Based on a recent systematic review on self-management interventions in people with PD (71) we identified two RCT’s (72, 73) that have studied a self-management intervention including lifestyle advice for people with PD using the PDQ-39 as an outcome. While the present intervention is much more comprehensive and personalized and includes more coaching and guidance when needed, we decided to conservatively use the results of those studies for our sample size calculation. Both studies found a mean between group difference of 4.15 on the PDQ-39, with a mean standard deviation of 10.55. With a significance level of 0.05 and 80%, we need 102 participants per group. Assuming 20% dropouts, we will include 128 participants per group (256 in total).

### Recruitment

2.9

We will apply a series of previously successful recruitment strategies. First, we will send an invitation to a panel of people with PD interested in research, who are subscribed to a mailing list of our research group. They have either shown interest in research by subscribing to the mailing list or by participating in one of our previous research projects. Second, we will exploit other options to reach potential participants, including advertising and blogging on social media (LinkedIn, Facebook, X, Instagram) and the online platforms of the Parkinson Vereniging (Dutch association for people with PD), giving presentations at local and regional patient support groups, recruiting patients at our outpatient clinic at the Center of Expertise for Parkinson & Movement Disorders at the Radboudumc, and using the regional PD professional network (i.e., the Dutch ParkinsonNet with national coverage). Furthermore, word-of-mouth recruitment is encouraged via current participants and community contacts. We aim to recruit a representative study population by using multiple complementary recruitment strategies, balancing targeted approaches to reach individuals with greater lifestyle-related needs with broader recruitment efforts to ensure sufficient statistical power within the limited timeframe of the trial (74).

### Randomization

2.10

#### Sequence generation

2.10.1

After completing the baseline questionnaires, eligible participants will be randomly allocated to the intervention group or the control group in a 1:1 ratio. Randomization will be performed in the data management system CastorEDC (75) using random block sizes (block sizes: 4, 6, 8). We will stratify the randomization based on disease duration, categorizing participants into three groups: <5 years, 5–10 years, and >10 years since disease onset. The randomization will be performed by a researcher who is not involved in the measurements and data analysis. The study is single-blinded. The researcher performing the analyses is not aware of treatment allocation.

### Data collection

2.12

#### Plans for assessment and collection of outcomes

2.12.1

The primary and most secondary outcomes in this study are collected through questionnaires completed by participants at home via the CastorEDC system. These questionnaires are sent to participants’ email addresses by the study’s researchers or assessors immediately after obtaining informed consent, and again after 6 and 12 months. Wrist sensor data will be collected by participants in their own environment. To promote data quality, the wrist sensor is accompanied by a step-by-step instruction. Additionally, the Empatica app provides real-time feedback to the participant to confirm whether the device is being worn correctly.

#### Plans to promote participant retention and complete follow-up

2.12.2

To support participant retention, updates are sent via email newsletters to all participants twice a year. The updates will be kept general to minimize deblinding. Furthermore, to promote compliance, participants in the control group receive the publicly available lifestyle decision aid, and an intake with the lifestyle coach as a starting point. They have access to the information in the decision aid throughout the intervention. Additionally, all participants are invited to the yearly symposium for people with PD organized by our center.

### Data management

2.13

Questionnaire data in this study is securely stored using CastorEDC, a certified data management system with a built-in audit trail. Data from the wrist monitor will be stored and made accessible through Empatica’s Carelab cloud environment, which is also certified and complies with relevant data protection (67). Within the Empatica environment, pseudonyms will be used for all participants, and no directly identifiable data will be collected or stored. Log data generated using the lifestyle decision aid is stored within the secure environment of Zorgkeuzelab (35), a member of the study consortium. This data is pseudonymized and Zorgkeuzelab does not have access to any personal information of the participants.

### Confidentiality

2.14

Personal information will be stored in the participant management software Salesforce (Salesforce, San Francisco, CA, United States). Access to this system is restricted to the research team and protected by secure password authentication. The participants receive a pseudonym that will be stored in PIMS, a local system in the Radboudumc to manage pseudonyms and identifiers in a secured and central way, separate from the research data. The informed consents and diagnosis confirmation will be collected and stored on paper in a fireproof and locked cabinet at the Radboudumc. The data collected in this study will be archived for 15 years after the study.

### Statistical methods

2.15

Descriptive statistics will be used to summarize baseline characteristics. Means, standard deviations, medians, ranges, counts, and percentages will be reported as appropriate, depending on the distribution and scale of the variable.

#### Methods for primary and secondary outcomes

2.15.1

##### Primary outcomes

2.15.1.1

The primary endpoint is the difference between groups in QoL (PDQ-39) over 12 months’ time. A linear mixed model (LMM) with repeated measurements will be used to evaluate the changes over time between the intervention and control group. The primary outcome and dependent variable is the total score of the PDQ-39, with additional models fitted for each of the eight domain scores. We include fixed effects for group, time (T0, T1 and T2) and the interaction between group and time. Sex, age, and disease duration at baseline will serve as covariates. Random effects will be included for participants to account for within-subject correlation and for lifestyle coaches to account for clustering by coach.

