**Methods:**

We will perform a 12-month single-blind randomized controlled trial. We aim to include 256 people with PD, randomized in a 1:1 ratio into a control and intervention group. Both groups receive a clinical assessment with a lifestyle coach and can partake in usual care. The intervention group receives an additional lifestyle intervention, consisting of guidance and interventions on different lifestyle domains: stress, exercise, nutrition, sleep and self-management (the SENSS approach). This intervention is offered remotely according to a stepped care model to personalize the intervention to the participants’ needs and abilities. The primary endpoint is the between-group difference in quality of life at 12 months (Parkinson’s Disease Questionnaire-39). Secondary endpoints include between-group differences in PD symptoms, health-related outcomes, self-management and personal goals. Cost-effectiveness and the experiences of participants and healthcare professionals will also be explored.

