#### Primary outcome

2.6.1

The primary outcome is the between-group difference in QoL from baseline to 12 months (end of intervention) measured with the Parkinson’s Disease Questionnaire-39 (PDQ-39) (44). The PDQ-39 is the most widely used QoL scale in PD, frequently used as the outcome measure, e.g., in trials on deep brain stimulation, multidisciplinary care and allied health interventions (45, 46). This questionnaire assesses the impact of PD on a person’s QoL. It consists of 39 questions across eight dimensions of daily living including relationships, social situations and communication. Item scores are filled out on a 5-point scale from “never” to “always.” Both the total score of the PDQ-39 and the scores for each of the eight dimensions are considered primary outcomes.

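### The primary endpoint is worded three ways with no deciding contrast named, and the stated model does not make full use of baseline PDQ-39

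*Protocol article*

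**What the plan says.** The protocol article defines the primary endpoint in three places:

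- Abstract, Methods: "The primary endpoint is the between-group difference in quality of life at 12 months".
- Section 2.6.1: "The primary outcome is the between-group difference in QoL from baseline to 12 months (end of intervention").
- Section 2.15.1.1: "The primary endpoint is the difference between groups in QoL (PDQ-39) over 12 months’ time".

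Section 2.15.1.1 then describes a linear mixed model for repeated measurements: "We include fixed effects for group, time (T0, T1 and T2) and the interaction between group and time". On covariates it says "Sex, age, and disease duration at baseline will serve as covariates". Random effects are planned for participants and for lifestyle coaches. Neither a random slope nor a residual covariance structure is mentioned. Section 2.15.3 adds maximum likelihood under missing at random.

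Section 2.8 plans on a difference of 4.15 with SD 10.55, a 0.05 level and 80% power. This gives 102 per group, or 128 per group with 20% dropout. It does not say whether 10.55 is an SD of scores or of changes.

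**The concern.** An analyst following the text could report any of several quantities as the primary result: the difference at T2, the difference in change from T0 to T2, a joint test of the group-by-time interaction, or an average over visits. The model can supply all of them and the text ranks none. If the choice is left until the data are seen, the primary p-value is not fixed in advance.

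The second issue is precision. T0 is measured before randomisation, so the true group means at T0 are equal. The stated model does not use this. It estimates a free group difference at T0 and does not list baseline PDQ-39 as a covariate. The trial already collects the measurement that would tighten the primary confidence interval.

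**Working it through.** **Inputs.** From section 2.8: difference 4.15, SD 10.55, α 0.05 (taken as two-sided), 102 evaluable and 128 randomised per group. The documents give no correlations between visits, so every ρ below is an assumption.

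**The plan's own figure.** n = 2 × 10.55² × (1.960 + 0.842)² / 4.15² = 101.4, so 102 per group; 102/0.8 = 127.5, so 128. Both reproduce. The size is that of a single comparison of two means (1 df).

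**What each wording means in the stated model**

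- At 12 months: group + group×T2.
- Change from baseline to 12 months: group×T2.
- Over 12 months: could be group×T2, the 2-df joint interaction, or an average over visits.

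**First against second.** The two estimates differ by the group coefficient, which is the observed T0 difference. If 10.55 is the SD of scores, its SD with 128 per group is 10.55 × √(2/128) = 1.32 points. The 95% range is ±1.96 × 1.32 = ±2.6 points, and 2.58/4.15 is 62% of the planned effect.

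**Third wording read as a joint test.** Assume score SD 10.55, correlations T0–T1/T1–T2/T0–T2 of 0.8/0.8/0.65, and 102 per group (noncentral chi-square).

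| True effect | T2 contrast | 2-df test |
|---|---|---|
| 2 points at T1, none at T2 | 5% | 73% |
| Linear growth to 4.15 at T2 | 92% | 86% |
| Linear growth, scaled so the T2 contrast has 80% | 80% | 71% |

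The first row is a constructed case. It shows that the two tests answer different questions.

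**Precision.** Per-arm variances with equal SD σ at T0 and T2: change contrast 2(1−ρ)σ²; baseline-adjusted contrast (1−ρ²)σ². The ratio is (1−ρ²)/[2(1−ρ)] = (1+ρ)/2. Power is for a difference of 4.15 at 102 per group.

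| ρ(T0,T2) | Variance ratio | 10.55 = SD of change: change → adjusted | 10.55 = SD of scores: change → adjusted |
|---|---|---|---|
| 0.5 | 0.75 | 80% → 90% | 80% → 90% |
| 0.6 | 0.80 | 80% → 88% | 88% → 94% |
| 0.7 | 0.85 | 80% → 86% | 95% → 98% |
| 0.8 | 0.90 | 80% → 84% | 99% → over 99% |
| 0.9 | 0.95 | 80% → 82% | over 99% → over 99% |

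**Covariance, conditional on a random intercept only.** Such a model gives every pair of visits the same correlation, about the mean r̄ of the three. With complete data and model-based standard errors, the ratio of modelled to true variance for T2−T0 is (1−r̄)/(1−r02), where r02 is the T0–T2 correlation. The type I error is 2[1−Φ(1.96√ratio)].

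| r01/r12/r02 | Variance ratio | Type I error |
|---|---|---|
| 0.70/0.70/0.70 | 1.00 | 5.0% |
| 0.75/0.75/0.70 | 0.89 | 6.5% |
| 0.80/0.80/0.70 | 0.78 | 8.4% |
| 0.70/0.70/0.49 | 0.73 | 9.5% |
| 0.80/0.80/0.64 | 0.70 | 10.0% |

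Simulation (20,000 runs, 102 per group) gave 8.3%, 9.4% and 9.9% for the last three rows. With the contrast's own variance, as an unstructured covariance provides, simulated rates were 4.5% to 5.0%.

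**The case against.** Four points can be made for the plan.

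- **One effect, not several.** Under randomisation the difference at 12 months and the difference in change have the same expected value. Section 2.15.1.1 speaks of evaluating changes over time, and section 2.15.1.2 compares changes from baseline to 12 months for the wrist-monitor data with the same model structure. Group×T2 is thus the natural reading, and no 2-df test is proposed anywhere. This stands: the text allows a joint test but does not plan one. It remains true that no sentence names the deciding contrast and that the two point estimates will differ.
- **Baseline is not ignored.** A reader might infer that the analysis fails to account for baseline and is biased. It is not: T0 is in the response vector, and group×T2 is a valid, unbiased change-score contrast. What is lost is precision.
- **Equal correlation is not imposed.** A reader might infer that the model forces equal correlation between visits and so inflates type I error. The text names only participant random effects. Intercept-only is a likely reading, not a stated one, and the covariance structure may be set in an analysis plan not shown. Inflation also needs decaying correlation and model-based standard errors, and it vanishes when correlations are equal.
- **The sample size is not wrong.** The stated figures reproduce, and no planned power is shown to be lost.

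**Conclusion.** The point holds as an inconsistency in the endpoint wording together with an inefficient model. The three definitions do not match and none names the deciding contrast. The at-12-months and change estimates would differ by chance with SD 1.32 points. The ±2.6 is a 95% range, not a maximum, and it assumes that 10.55 is a score SD. The group×T2 contrast is unbiased, but its variance can be cut by 5% to 25% for assumed ρ of 0.9 to 0.5. Power at 102 per group would rise from 80% to between 82% and 90% if 10.55 is the SD of change. If it is the SD of scores, power would rise from 80% to 90% at ρ 0.5 and from 88% to 94% at ρ 0.6.

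The covariance issue is a conditional safeguard, not an error in the document. Type I error would be about 6.5% to 10% in the assumed decaying patterns under an intercept-only model, and 5% under equal correlations.

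**What to change.** 1. Name one primary estimate: the between-group difference in PDQ-39 total score at T2. Use the same wording in the abstract, section 2.6.1 and section 2.15.1.1.
2. Handle baseline in one of two ways. Either keep T0, T1 and T2 as responses with categorical time and a common T0 mean (drop the group main effect, keep group×T1 and group×T2). Or use T1 and T2 as responses with T0 PDQ-39 × time as covariate. Do not add baseline as a covariate while T0 stays a response.
3. Test the T2 contrast only, and report T1 as secondary.
4. As a safeguard, state an unstructured 3×3 covariance for the three visits (2×2 if only T1 and T2 are responses).

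The cost is wording: no new data, and six covariance parameters are easily estimated with 256 participants. The Trial status section reports 219 randomised and none finished at 20 November 2025, so at that date the primary estimate could still be fixed before any participant had completed the study. Section 2.15.1.2 reuses the model structure for the secondary outcomes, so the model correction carries over to those measured on the same schedule.

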##### Secondary outcomes

2.15.1.2

The secondary analyses will evaluate the between-group difference in secondary outcomes (Table 1) over 12 months using the same LMM structure as the primary analysis. In addition, the raw wrist monitor accelerometer and PPG data collected at baseline and at 12 months (each for a one-week period) will be processed to derive information on physical activity and sleep. We will use algorithms developed in-house at the Radboudumc (76) and in collaboration with Eindhoven University of Technology (TU/e) (77) to process the raw data into interpretable metrics such as total physical activity, sedentary behavior, sleep duration and sleep quality. After processing the data, average values across the one-week periods will be calculated per participant at each timepoint. The within-subject changes from baseline to 12 months will be compared between groups using a LMM with the same structure as the primary and other secondary analyses.

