There are also a few potential challenges we anticipate. First, there is a risk of limited external validity. Individuals already interested in lifestyle interventions are more likely to enroll, while those less interested may be harder to reach. Analysis of participants in previous studies at our center indicates that the sex distribution aligns with the Dutch PD population, but older adults and non-native Dutch individuals are underrepresented (80). We aim to include people across all age categories and socio-economic backgrounds. This is particularly challenging since the approach is mainly based on eHealth, and offered in Dutch. To address this, we capitalize on our rich experience around diversity when including participants (81–83). We will implement proactive strategies such as targeted outreach to underserved populations and selective advertising. Additional measures include offering technical support and providing paper-based alternatives for the assessments when necessary. Moreover, due to the personalized nature of the intervention, it can be tailored to the individual participant’s needs and abilities. Second, there is a risk of selection bias. Since the control group will not receive any intervention after the intake at the start of the study, we anticipate an increased dropout risk in this group. We aim to prevent this by keeping them involved with the study by sending them biannual newsletters and invitations to the yearly symposium for people with PD organized by our center. Also, we decided to give these participants access to the information in the lifestyle decision aid, to promote compliance (84). Furthermore, we kept the burden of assessments low by performing them fully remote, restricted to questionnaires and a wrist monitor that will be sent to people’s homes. Third, there is a potential risk of contamination between the intervention and the control group. Blinding of the participants is difficult in an intervention study using a non-pharmacological intervention. We will try to get as close to blinding as possible by minimizing information about the intervention for the control group, and by naming the groups the guided and independent lifestyle interventions. We expect the impact of possible contamination to be minimal, because it is difficult to keep up with a behavioral change on the long term without (structural) guidance (85). At the end of the study, participants will be asked to indicate which group they believe they were allocated to, in order to assess the impact. Also, the control group only has access to the publicly available tools and therefore not to all tools used in the intervention group. Importantly, our present approach will reveal how the proposed intervention performs, over and above current clinical situation, including the ability of people with PD to access the available interventions themselves.

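### On its natural reading, the primary model does not adjust the baseline-to-12-month PDQ-39 contrast for the randomisation stratum when data are complete; covariate-by-time terms would be a cheap improvement

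*Protocol article*

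**What the plan says.** Section 2.15.1.1 fits one linear mixed model to PDQ-39 at baseline, 6 and 12 months. The fixed effects are given as: "We include fixed effects for group, time (T0, T1 and T2) and the interaction between group and time". The covariates follow: "Sex, age, and disease duration at baseline will serve as covariates". The random part reads: "Random effects will be included for participants to account for within-subject correlation and for lifestyle coaches to account for clustering by coach". No covariate-by-time term is named. The text does not say main effects only, but that is the natural reading of a list with a single interaction.

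Section 2.6.1 defines the primary outcome as a between-group difference from baseline to 12 months, which points to the group-by-T2 term. The abstract words it differently: "The primary endpoint is the between-group difference in quality of life at 12 months".

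On randomisation, 2.10.1 says: "We will stratify the randomization based on disease duration, categorizing participants into three groups" (<5, 5–10 and >10 years). Section 2.15.1.2 analyses the secondary outcomes "using the same LMM structure as the primary analysis".

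Section 2.15.3 relies on maximum likelihood under missing at random. Section 2.8 allows for 20% dropout. Of the control group the Discussion says: "we anticipate an increased dropout risk in this group".

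**The concern.** A reader of 2.15.1.1 would take the primary effect to be adjusted for the stratification factor, age and sex. When baseline is itself a response and the effect is a change, a covariate that is constant over time and not crossed with time can explain differences in level between people. It cannot explain differences in change, and the treatment effect is a difference in change.

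Two things are at stake:

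- **Precision.** If disease duration, age or sex predict how PDQ-39 moves over 12 months, the model as written leaves that variation in the residual.
- **Robustness to dropout.** Maximum likelihood under missing at random is valid for the mean model that is fitted. A model that forces the same time course on every stratum can be off when strata differ in change and are lost at different rates in the two arms.

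**Working it through.** **Inputs from the protocol.** Effect 4.15, SD 10.55, alpha 0.05, power 80%, 102 then 128 per group, 20% dropout (2.8); 1:1 allocation stratified by duration (2.10.1); model terms (2.15.1.1).

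**The plan's own figure.** n = 2 × (1.960 + 0.842)² × (10.55/4.15)² = 2 × 7.849 × 6.463 = 101.5, so 102 per group. Then 102/0.80 = 127.5, so 128 per group and 256 in total. This reproduces (two-sided alpha).

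**Algebra.** Write the model for person i at visit t as

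Y_it = b0 + b1·G_i + τ_t + δ_t·G_i + γ′X_i + u_i + e_it.

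Then Y_i2 − Y_i0 = τ_2 + δ_2·G_i + (e_i2 − e_i0), with τ_0 = δ_0 = 0. Both γ′X_i and the person effect are gone. A coach intercept is also constant over visits and cancels in the same way. With complete data δ_2 is the raw difference in mean change, whatever is in X.

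**Numerical check, complete data.** 256 simulated participants, three visits, random participant intercept, true effect −4.15, residual change SD 10.55 (taking the SD in 2.8 as a change SD is an assumption); coach effect left out. One data set:

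| Covariates | Group × T2 | SE | Between-person variance | Residual variance |
|---|---|---|---|---|
| None | −4.2413 | 1.3540 | 120.9 | 58.67 |
| Main effects | −4.2413 | 1.3540 | 83.8 | 58.67 |
| Crossed with time | −4.2323 | 1.3017 | 85.3 | 54.07 |

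Main effects reduce only the between-person variance. The SE of the change contrast rests on the residual variance: √(2 × 58.67 × 2/128) = 1.354. A second simulated data set gave −1.507193 (SE 1.29163) both without covariates and with main effects, and −1.569 (SE 1.287) with crossing.

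**Precision forgone.** 1 − 1.3017/1.3540 = 3.9% in the first data set and 1 − 1.287/1.29163 = 0.4% in the second. Averaged over 400 data sets it was 1 − 1.31/1.33 = 1.5%.

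**Dropout, by hand.** Assume stratum shares 45/35/20%, mean 12-month worsening of 0/3/6 points by stratum, the same treatment effect in each stratum, control dropout 10/30/60% and intervention dropout 15% throughout.

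- Mean worsening, all randomised: 0.35×3 + 0.20×6 = 2.25.
- Control completers: (0.35×0.7×3 + 0.20×0.4×6)/(0.45×0.9 + 0.35×0.7 + 0.20×0.4) = 1.215/0.73 = 1.66.
- Intervention completers: 2.25.
- A completers' contrast is off by 2.25 − 1.66 = 0.59, against the intervention.

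If dropout is 10/25/35% in both arms, completers' worsening is (0.2625×3 + 0.13×6)/0.7975 = 1.97 in each arm and the difference is zero.

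**Dropout, by likelihood.** Same shares, half of dropouts also missing T1, 400 data sets per row, Monte Carlo error about 0.07–0.08. Entries are bias in PDQ-39 points; positive means benefit is understated.

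| Change by stratum | Dropout control / intervention (%) | No covariates | Main effects | Crossed with time |
|---|---|---|---|---|
| 0/0/0 (level only) | 10/30/60 v 15/15/15 | +0.25 | −0.03 | −0.01 |
| 0/1.5/3 | 10/30/60 v 15/15/15 | +0.48 | +0.18 | −0.04 |
| 0/3/6 | 10/30/60 v 15/15/15 | +0.80 | +0.46 | +0.02 |
| 0/3/6 | 10/30/50 v 30/15/5 | +1.09 | +0.64 | +0.08 |
| 0/6/12 | 10/30/60 v 15/15/15 | +1.19 | +0.78 | −0.10 |
| 0/3/6 | 10/25/35 in both arms | −0.10 | −0.11 | −0.12 |

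A milder set of assumptions used 1–2 points more worsening per SD of age and 0.75–1.5 per duration stratum. Control dropout was 20–30%, rising with age (odds ratio 1.6–2.7 per SD), and intervention dropout 10–20%, unrelated to age. The main-effects model then had 0.08–0.41 points more bias than the crossed model.

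**The case against.** The strongest reply is that the article is condensed. It never says main effects only, and covariate-by-visit terms could sit in an analysis plan that is not shown. That stands as a caution. The point is about the model as listed, and how disease duration is coded there is missing detail, not an error.

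A reader might go further and infer that the primary result is in effect unadjusted and open to bias whenever dropout depends on a covariate. The documents do not support that, for four reasons:

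- Exact cancellation needs complete data, while the bias needs dropout. Once visits are missing, main effects enter the likelihood. They removed the bias when the stratum affected level only, and about a third to two thirds of it when the stratum affected change (for example +0.80 to +0.46, or 43%).
- Covariate-related dropout alone is not enough. Equal dropout by stratum in both arms gave no detectable bias in any model. The Discussion expects more control dropout but ties it to no covariate.
- Stratified allocation balances duration whatever the model, so the complete-data contrast is unbiased.
- If the effect is read as the difference at 12 months, as the abstract words it, main effects do adjust it (−5.06 to −5.24 in the first simulated data set). Likewise, if the wrist-monitor changes in 2.15.1.2 are themselves the response, main effects adjust them directly.

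All four stand. They limit the point but do not remove it: the listed model cannot represent change that depends on duration, age or sex.

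**Conclusion.** The concern holds in a limited form. For the baseline-to-12-month contrast, read from group-by-time with covariates as main effects, the covariates and the randomisation stratum do nothing when data are complete. That part is exact. The cost there is precision only, about 0–4% of the SE, and only if the covariates predict change.

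With dropout the main effects adjust in part. Residual bias needs two conditions together: a covariate predicts PDQ-39 change, and its relation to dropout differs by arm. In the adverse scenarios tried, the bias was about 0.1–0.8 points, or 2–19% of 4.15 (0.1/4.15 and 0.78/4.15). It was against the intervention, but that direction follows from the scenarios chosen. Stratum shares, differences in change and dropout patterns are all assumptions; the protocol gives none of them. The point is a cheap improvement of minor weight, not an error that threatens the trial's conclusion.

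**What to change.** In 2.15.1.1, replace the covariate sentence with wording such as:

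> The randomisation stratum (<5, 5–10, >10 years, as used at randomisation), age and sex enter the model, each with its interaction with categorical time (T0, T1, T2). The 12-month group contrast is reported averaged over the observed covariate distribution.

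The same then applies through 2.15.1.2 to secondary outcomes for which T0 is a response. This form adjusts the 12-month comparison under either wording of the endpoint.

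**Cost.** Up to about 8 extra model degrees of freedom (4 covariate terms × 2 follow-up visits) in 256 participants, and an SE about 1% larger if the covariates turn out not to predict change (in the level-only scenario the empirical SD was 1.49 against 1.47). No new data are needed. The Trial status section reports that no participant had finished by 20 November 2025, so the wording could be fixed before 12-month results are analysed.
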